## Abstract

Knee osteoarthritis is a common chronic degenerative joint disease in middle-aged and elderly people. Intra-articular injection for the treatment of knee osteoarthritis is a regularly utilized nonsurgical treatment in modern medicine. Hyaluronic acid (HA) and platelet-rich plasma (PRP) are two frequently employed intra-articular devices. Hyaluronic acid (HA) is an accepted nonsurgical treatment for symptomatic KOA, and platelet-rich plasma is a popular option in the treatment of KOA in recent years. The purpose of this research is to compare the efficacy and safety of intra-articular injection of platelet-rich plasma (PRP) versus hyaluronic acid (HA) on the pain score scale, knee function, and related inflammatory biomarkers in KOA patients using a clinical randomized controlled trial. Participants are being randomized into either the hyaluronic acid (HA) or into the platelet-rich plasma (PRP) group. All patients receive 4 weeks of treatment (once a week), and well-being support and quadriceps training (3 times a week). The primary outcomes are measured using the Western Ontario and McMaster Universities Osteoarthritis Index (WOMAC) and the visual analog scale (VAS). The secondary outcomes include the activities of daily living score, erythrocyte sedimentation rate, C-reactive protein testing, interleukin-6 levels, and X-ray examination. In order to monitor the occurrence of irregularities and abnormalities, patients are assessed at each visit, and restorative treatment is given if necessary. The results of this clinical trial will verify the efficacy of PRP and HA in the treatment of KOA and provide important evidence for the clinical treatment of KOA. The trial was enlisted at the Chinese Clinical Trial Registry on 26 September 2020 (ChiCTR2000038635).

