## 2. Methods

### 2.1. Study Design and Setting

This is a prospective randomized controlled superiority clinical trial to assess the adequacy and security of intra-articular injection of PRP and intra-articular injection of HA for knee osteoarthritis. This overview was conducted at the General Hospital of Ningxia Medical University. A total of 70 participants with knee osteoarthritis are being randomly allocated to the PRP and HA groups at a 1 : 1 ratio. Prior to initiation of the study, all subjects complete daily activity tests after a questionnaire asking for detailed medical history. All study participants are required to sign a written informed consent prior to participation. The study includes assessments at the following time points: before intervention, 1 month after intervention, and after a further follow-up period of 3 and 6 months with no active intervention (Figure 1).

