### 2.4. Inclusion Criteria

Patients are eligible qualify if they fulfill the clinical American College of Rheumatology knee OA criteria. Other inclusion criteria are as follows: (1) aged 40–75 years, (2) graded II-III of Kellgren–Lawrence Radiographic Classification, (3) VAS score of knee joint pain is above 4 out of 10, (4) have received no medication or relevant treatment in the last 3 months, and (5) volunteer to take an interest in the investigation and sign the informed consent.

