### 2.11. Quadriceps Muscle Training

All patients begin quadriceps muscle training 24 hours after the intervention, and the training is conducted under the guidance of the therapist. Before each treatment, the preparatory activities, mainly including lower limb active exercise and knee flexor and extension exercise, is conducted for 3–5 minutes. Quadriceps femoral training method: (1) Isometric training: squat training: the patients position the back against the wall with the body straight and feet slightly wider than the shoulders. With toes facing front, the patients slowly squat using both legs for a duration of 2–5 minutes and a total of 5–10 times. Participants must make sure they stand slowly and rest for 5–10 seconds between each squat. (2) Isotonic training: a quadriceps training chair is used for this exercise. The patients take the sitting position and refrain from moving their legs whilst stretching and bending their knee 10 times each for 1 group. There are a total of 6 groups for each training session, with a rest period of 2 minutes between groups. Weight training is also carried out base on standard according to the patient's muscle strength. The weight is gradually increased until the patient can complete the required training volume. The above quadriceps muscle training lasts for 20 minutes each time, once a day, for a total of three times a week. Quadriceps muscle training is ongoing with the whole study process and requires the subjects to keep exercising consistently outside the hospital.

All results are assessed by experienced evaluators who have been trained and specifically allocated to manage these evaluations. Results are randomized blind in accordance after each of the standard visits. Each patient is evaluated by the same evaluator for every stage of the evaluation.

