### 2.12. Primary Outcome

VAS score [22]: the VAS score is used to assess knee joint pain. It is usually a flat line, 100 mm in length, anchored by word descriptors at each end. Patients mark the point on the line of current pain. The VAS score is then decided by measuring in millimeters from the left end of the line to the point that the patient marked. Patients can experience pain ranging from no pain to extreme pain. The higher the score, the severer the pain. The VAS score is measured during all the assessment visits.Western Ontario and McMaster University Bone joint Index (WOMAC) Scoring System [23]: the WOMAC scale specifically includes 24 questions in three aspects of joint pain, stiffness, and functional limitation. Each question consists of five levels of pain: none, mild, moderate, severe, and very severe. The lowest score for WOMAC is 0, and the highest score is 96 for each item. The higher the score, the worse the joint function.

Variations in VAS scores and WOMAC functional scores for each patient are compared and analyzed at specified time points between groups along with the comparison of the average scores among groups.

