### 2.15. Statistical Analysis

The SPSS 26.0 software is used for data analysis. All quantitative data are indicated by the percentile calculator. The chi-square test is used if the measurement data are normally distributed, and the data are expressed as mean ± standard deviation. The independent sample *T*-test is utilized to compare the mean values of the two groups. If the measurement information does not adjust to the normal distribution, the interquartile spacing is described and the independent sample Mann-Whitney *U* test is utilized. To assess changes within and between groups, we perform an analysis of variance (ANOVA) on repeated measures. Intentionality analysis and multiple interpolation are used to complete the missing values, and intentionality analysis and conforming protocol analysis are used to determine the sensitivity of the inflammatory outcome efficacy indicators. Statistical significance is assumed *P* less than 0.05.

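### The abstract promises to confirm that both PRP and HA work, and 2.15 tests change within groups, but two injected arms with no control support only a PRP versus HA conclusion

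*Protocol article*

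**What the plan says.** The abstract closes on the expectation that "The results of this clinical trial will verify the efficacy of PRP and HA in the treatment of KOA". Section 2.1 describes the design: "This is a prospective randomized controlled superiority clinical trial", and "A total of 70 participants with knee osteoarthritis are being randomly allocated to the PRP and HA groups at a 1 : 1 ratio". No third arm is mentioned anywhere.

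Section 2.15 states: "To assess changes within and between groups, we perform an analysis of variance (ANOVA) on repeated measures". It ends with one significance threshold, P<0.05, and does not separate the within-group results from the between-group ones.

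Four other features bear on how change within an arm can be read:

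- **Entry.** Section 2.4 requires that "VAS score of knee joint pain is above 4 out of 10". Section 2.12 makes VAS a primary outcome, and "The VAS score is measured during all the assessment visits".
- **Training.** Section 2.11: "All patients begin quadriceps muscle training 24 hours after the intervention". It continues throughout the study.
- **Education.** Section 2.7 provides health education to both groups.
- **Blinding.** Section 2.8 says participants are not blinded.

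**The concern.** The design estimates one randomized quantity: PRP minus HA, with education and training given to everyone. The abstract claims something else, namely that each product works. To show that, each arm would have to be compared with what the same patients would have experienced without an active injection, and no arm supplies that comparison.

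The planned within-group analysis looks like a substitute but is not one. Patients chosen for a high score on an outcome tend to score lower when measured again. Exercise and education are started in everyone, and the Introduction itself lists both among current treatments for knee OA. Unblinded patients report their own pain. Each of these can lower scores in both arms with no contribution from the injection.

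At stake is what the trial may conclude. A small P value for change over time could be read as support for the abstract's claim when it carries no such information.

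**Working it through.** **1. What the stated sample size was built for.** Section 2.2 gives 35 per arm, 20% dropout, 80% power and a 0.05 significance level. It states no effect size or SD, so the figure cannot be reproduced forwards. Working backwards, 35 × 0.8 = 28 evaluable per arm. At two-sided 0.05 (the sidedness is assumed), the detectable standardized difference is (1.96 + 0.84) × √(2/28) ≈ 0.75. The number is thus compatible with a between-arm comparison.

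**2. Assumptions for the illustration.** The documents give only the threshold of 4 and the 28 evaluable per arm. Assumed: VAS in the screened population is normal with SD 2, the mean and test-retest correlation ρ vary as below, and the injections are inert.

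**3. Fall in mean VAS from regression to the mean.** With a = (4 − μ)/SD,

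fall = (1 − ρ) × SD × φ(a) / (1 − Φ(a)).

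- μ = 4, ρ = 0.5: 0.5 × 2 × 0.399/0.500 = 0.80 point.
- μ = 6, ρ = 0.8: 0.2 × 2 × 0.242/0.841 = 0.12 point.
- μ = 3.5, ρ = 0.6: 0.4 × 2 × 0.387/0.401 = 0.77 point.
- μ = 5.5, ρ = 0.8: 0.2 × 2 × 0.301/0.773 = 0.16 point.

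**4. How often a within-arm test is significant.** This was simulated with a paired t test, two-sided 0.05, n = 28 per arm and 4,000 replicates per scenario. The nominal rate in the direction of improvement is 2.5%.

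| Shared training effect (assumed) | μ 4, 5, 6; ρ 0.5, 0.7, 0.8 | μ 3.5, 4.5, 5.5; ρ 0.6, 0.7, 0.8 |
|---|---|---|
| None | 6.5% to 60.5% | 10% to 65% |
| 0.5 point | 56% to 95% | 68% to 97% |
| 1.0 point | 93% to 100% | 98% or more |

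With all 35 per arm retained, the ranges on the first grid are 7% to 71%, 67% to 98% and 97% to 100%.

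**5. Both arms significant together.** The abstract's claim concerns both products. On the first grid with n = 28, both arms reach P<0.05 in 0.5% to 37% of trials with no training effect, 31% to 90% with 0.5 point and 87% to 100% with 1.0 point.

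**6. The randomized contrast.** In the same simulations, the two-sample test of change between arms rejects in 4% to 6% of trials in every scenario, which is its nominal level. Regression to the mean and shared training cancel between arms.

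**The case against.** The strongest reply is that the trial is already comparative. The abstract, the Introduction, section 2.1 and the Discussion all state a PRP versus HA purpose. Section 2.12 compares VAS and WOMAC between groups, and section 2.15 uses two-sample tests. On this view the fault is one loosely worded sentence, and no section says that a within-group P value establishes efficacy. Much of this stands: the superiority comparison needs no change. But the sentence is the conclusion the article announces, and section 2.15 plans a test that would appear to support it.

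A second reply is that HA is an accepted active comparator, so PRP superiority would support PRP. The Introduction does treat HA as effective, and on that premise the argument has force for PRP. It cannot confirm HA, however. The Discussion calls the safety and efficacy of both injections controversial, and a null difference would confirm neither.

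Several stronger readings are tempting and should not be made:

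- **That within-arm significance is nearly certain whatever the injections do.** Regression to the mean alone can be modest, and section 2.5 excludes acute knee OA pain, which plausibly limits selection at a transient peak. Near-certainty needs an added shared effect, whose size is assumed here.
- **That three months without treatment lowers scores.** The requirement to "have received no medication or relevant treatment in the last 3 months" is an eligibility criterion. It is not shown to be a withdrawal period and does not in itself produce improvement.
- **That a null PRP versus HA result will be reported as both products working.** Nothing in the protocol says so. It is a risk that the wording leaves open.
- **That the figures carry over to WOMAC.** Entry has no WOMAC threshold, so regression there would be indirect and weaker. It was not simulated.

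**Conclusion.** The concern holds for the efficacy conclusion and for the within-group P value, and no further. With two injected arms, shared education and training, unblinded participants and selection on a primary outcome, within-arm change cannot be attributed to PRP or to HA. That conclusion follows from the design and needs no numerical assumption.

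The size does need assumptions. For VAS, with SD 2, ρ of 0.5 to 0.8 and 28 per arm, inert injections would show a significant within-arm improvement in roughly 6% to 65% of trials from regression to the mean alone, and in roughly 56% to 100% with a shared training effect of 0.5 to 1.0 point. The protocol gives none of the population means, SD, correlation or training effect, so these ranges show the mechanism and are not a forecast for this trial.

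A reader might infer that the PRP versus HA comparison is compromised too. It is not: neither regression to the mean nor training common to both arms disturbs it.

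**What to change.** - **Abstract.** Replace the efficacy claim for each product with the difference between PRP and HA on a background of education and training.
- **Section 2.15.** Base efficacy inference on the between-group contrast, either the group-by-time term or a baseline-adjusted comparison. Report within-group change as a mean with a confidence interval, without a P value.
- **Interpretation.** State that a non-significant between-group result will not be read as showing that either product is effective.

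The cost is wording only, with no new arm, patients or data. The trial gives up a claim it cannot support.

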## 1. Introduction

Knee osteoarthritis (OA) is a chronic, progressive, degenerative joint disease characterized by cartilage degeneration, osteophytes, subchondral sclerosis, and synovitis of the knee [1]. According to the World Health Organization (WHO), knee OA is the fourth most common debilitating disease in the world [2]. The overall prevalence of joint disease in the United States is about 15%, of which knee OA accounts for more than 40% [3]. Relevant statistics show that the rate of knee OA is higher than 50% in individuals over the 60-year-old in China [4]. The essential clinical manifestations of knee osteoarthritis are knee pain, standing difficulties, and severe disability with swelling, deformity, contractures, and muscular atrophy [5]. The disease has a devastating impact on quality of life and imposes a heavy burden on individuals, families, and societies. Therefore, knee osteoarthritis has been officially recognized as a major public health crisis [6].

Current treatment strategies for knee OA include basic health education, oral anti-inflammatory drugs, exercise therapy, physical therapy, topical anti-inflammatory gels, and intra-articular injections [7, 8]. Intra-articular injection is usually the last treatment option before surgical intervention and includes intra-articular corticosteroids or platelet-rich plasma (PRP) or hyaluronic acid (HA).

Hyaluronic acid (HA), the main component of the extracellular matrix, is a polysaccharide composed of glucosamine. Also known as a physiological lubricant for synovial joints, it promotes cell migration and proliferation, possesses anti-inflammatory properties, and regenerates tissue [9, 10]. Experts agree that hyaluronic acid is an effective method for treating knee OA [11], and there is sufficient evidence that hyaluronic acid can effectively relieve pain and improve knee function. Animal experiments have shown that HA plays an important role in anti-inflammatory, antiapoptotic, antiangiogenic, and antifibrosis [12]. A large number of clinical studies have shown that HA injection in patients with KOA can reduce joint pain and improve joint function and quality of life [13].

Platelet-rich plasma (PRP) is an autologous blood product rich in a variety of growth factors. Due to the fact that it contains a large number of growth factors, inflammatory mediating factors, and proteins, it promotes the proliferation of human synovium and chondrocytes to repair damaged cartilage tissue [14, 15]. Current studies demonstrated that intra-articular PRP injection produces greater and longer-lasting improvements in most of the outcome parameters compared to HA [16–18]. Increasing attention is being paid to the use of PRP in the treatment of osteoarthritis. In the past, reports on the efficacy of PRP or HA injection of knee OA mostly focused on the evaluation of clinical efficacy, while there were relatively few basic studies and reports on the changes of the levels of inflammatory cytokines in patients after joint cavity injection.

The onset and progression of osteoarthritis is believed to be associated with inflammation, even in the early stages of the disease. TNF-*α* and IL-6 are important cytokines involved in joint synovitis and cartilage matrix degradation [19]. CRP and ESR levels were positively correlated with OA severity [20]. In this study, patients in the PRP group receive intra-articular injection of PRP combined with quadriceps training; Patients in the HA group receive intra-articular injection of HA combined with quadriceps training. The purpose of this study is to compare the clinical and biological effects of intra-articular injection of PRP versus intra-articular injection of HA in patients with mild to moderate knee OA. The objective of the trial is to determine the clinical viability of PRP within the treatment of knee OA and to provide clinical evidence.

## 2. Methods

### 2.1. Study Design and Setting

This is a prospective randomized controlled superiority clinical trial to assess the adequacy and security of intra-articular injection of PRP and intra-articular injection of HA for knee osteoarthritis. This overview was conducted at the General Hospital of Ningxia Medical University. A total of 70 participants with knee osteoarthritis are being randomly allocated to the PRP and HA groups at a 1 : 1 ratio. Prior to initiation of the study, all subjects complete daily activity tests after a questionnaire asking for detailed medical history. All study participants are required to sign a written informed consent prior to participation. The study includes assessments at the following time points: before intervention, 1 month after intervention, and after a further follow-up period of 3 and 6 months with no active intervention (Figure 1).

### 2.2. Sample Size Calculation

In this strategy, WOMAC pain score reduction was concluded to be the most relevant indicator based on a previous study conducted by Vaquerizo et al. [21].

The test measure was evaluated using PAS 24.0 criteria, and the total number was set at 70 cases, specifically 35 cases in each group (permitting 20% dropout rate). The power is 80%, and the level of significance is 0.05. The overall sample size is anticipated to be 70 patients (35 in each group) (Table 1).

### 2.3. Participants and Recruitment

A total of 70 participants are being enlisted from the community in Yinchuan, Ningxia Hui Independent Locale, China. Participants are enlisted through multimodal procedures, print notices, WeChat, volunteer proposal, and community exposure. All participants undergo a standard assessment, consisting of a complete sociodemographic and clinical data collection. Prior to this, all participants are asked to read and sign the informed consent.

### 2.4. Inclusion Criteria

Patients are eligible qualify if they fulfill the clinical American College of Rheumatology knee OA criteria. Other inclusion criteria are as follows: (1) aged 40–75 years, (2) graded II-III of Kellgren–Lawrence Radiographic Classification, (3) VAS score of knee joint pain is above 4 out of 10, (4) have received no medication or relevant treatment in the last 3 months, and (5) volunteer to take an interest in the investigation and sign the informed consent.

### 2.5. Exclusion Criteria

Patients who (1) have autoimmune arthropathy; (2) have acute pain of knee OA; (3) have bleeding diathesis or a coagulation disorder; (4) have had a knee joint infection, surgery or radiation therapy within the last three months; (5) have had an injection of glucocorticoid or sodium hyaluronate within the last three months or have had an infection of the skin in an injection area; (6) pregnant and lactating women; (7) pretreatment radiographic KL grade reached IV; (8) suffer from serious organ failure, serious cardiovascular and cerebrovascular diseases, blood diseases or infectious diseases; (9) are participating in other trials that influence the results of this study; and (10) are allergic to eggs or HA proteins were exluded from this study.

### 2.6. Withdrawal Criteria and Management

Participants are allowed to withdraw or are asked to withdraw from the study, if (1) the patient has knee pain that cannot be relieved by intra-articular injection (>8 on the VAS score). In this event, the physician evaluates its severity and terminates the study if necessary. (2) In the event of a serious adverse circumstance such as a severe infection, being in a coma, going into shock, or death, the lead investigator will be contacted imminently and the study will be discontinued with immediate effect. (3) Subjects decide to discontinue treatment at any time and for any reason.

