### 2.7. Randomization and Allocation

After meeting the inclusion criteria, 70 qualified participants are being randomly allocated to either the PRP group and the HA group in a 1 : 1 allotment proportion. The irregular grouping sequence is performed concurring to an irregular list of numbers produced by the randomization center of Ningxia Medical University. It is hidden in an opaque sealed envelope.

The random sequence is overseen by particular personnel who have no contact with participants and are not included in the information collection or analysis. All qualified participants receive the following administrations free of charge, assessment, X-ray examination, health education, and quadriceps femoral training (both HA group and PRP group). All participants are strongly advised to follow up all evaluation and treatment plans as much as possible.

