### 2.9. PRP Injection Method

The patient is in the supine position with the affected knee flexion: 70°–80° and the feet in the neutral position. For local disinfection, the lower edge of the patella and 1 cm inside and outside of the patellar ligament (internal and external genicus) are selected as puncture points, which are used alternately. A disposable syringe is used to puncture into the joint cavity and 5 ml of the preprepared autogenous PRP is injected. If the joint effusion is present, the effusion is extracted first. After injection, the knee joint undergoes exercise on a passive range of motion and is observed for 20–30 minutes to determine that the subjects have no discomfort. For the first two days, participants are asked to do some light physical activity, limit weight on the affected lower limbs, and use ice packs for 10 minutes every eight hours a day. For mild to moderate pains, a maximum of four 500 mg acetaminophen tablets is permitted, and acetaminophen plus codeine is recommended if/when the pain persisted. With the exception of these painkillers, other drugs are not permitted for up to five days after injection. PRP joint injection is performed once a week for a total of 4 times.

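### The withdrawal rule in section 2.6 merges stopping treatment with leaving the study, so later VAS and WOMAC scores can be lost because pain was poor; the effect is probably small and cheap to prevent

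*Protocol article*

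**What the plan says.** Section 2.6 opens with "Participants are allowed to withdraw or are asked to withdraw from the study" and then gives three grounds. The first is that "the patient has knee pain that cannot be relieved by intra-articular injection (>8 on the VAS score"); in that event "the physician evaluates its severity and terminates the study if necessary". The second is a serious adverse event and is not at issue here. The third reads "Subjects decide to discontinue treatment at any time and for any reason".

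Other parts of the article bear on this:

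- Section 2.12 makes VAS and WOMAC the primary outcomes and states that "The VAS score is measured during all the assessment visits". Table 1 places those measurements at enrolment and at weeks 4, 12 and 24, with none during the injection weeks.
- Injections are weekly, four in all (sections 2.9 and 2.10). Section 2.1 describes what follows as "a further follow-up period of 3 and 6 months with no active intervention". Section 2.11, however, continues quadriceps training throughout the study.
- Section 2.9 allows acetaminophen after an injection, and "acetaminophen plus codeine is recommended if/when the pain persisted".
- Section 2.7 adds general advice: "All participants are strongly advised to follow up all evaluation and treatment plans as much as possible".
- Section 2.15, in rough English, plans what I read as intention-to-treat analysis with multiple imputation, plus a per-protocol analysis.
- Section 2.16 and Table 1 record increased pain as an adverse event, and the reasons for dropout and withdrawal.

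**The concern.** Two separate decisions share one list. Stopping a treatment is a clinical decision. Ending outcome collection is a decision about data. Section 2.6 ties the second to the first, and for ground (1) the link is a high value of a primary outcome. The patients most likely to lose their later scores are therefore those doing worst.

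An imputation model fitted to the patients who stay will fill in leavers' scores too favourably, unless it contains the score that made them leave. Both arms would then look better than they would without rescue. If more patients cross the threshold in one arm than in the other, the PRP-HA difference shifts as well. The lost visits are already scheduled, so the loss is avoidable.

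**Working it through.** **Step 1: what the text fixes.** Both grounds (1) and (3) complete a sentence about leaving the study. The article does not provide for VAS and WOMAC to continue after either event. The advice in section 2.7 is general and does not override a specific rule. The merging is therefore stated by the rule itself and is not inferred from silence.

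**Step 2: when it can cause bias.** If the trigger is a scheduled score, such as week 4, it is on file and can enter the imputation model. If the trigger falls in the injection weeks or between visits, Table 1 schedules no VAS there, and the article does not say whether the triggering score is kept. Only an unrecorded or unused trigger matters.

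**Step 3: size.** The article gives no VAS mean, SD, correlation or withdrawal rate, so every input below is an assumption, except the entry limit (section 2.4, above 4 of 10) and the threshold (section 2.6, above 8).

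- Baseline mean 6.5, SD 1.5; later SD 2; scores clipped to 0-10.
- Mean change at week 24: -1 for HA and -2 for PRP, so the true difference is about -0.99 after clipping.
- Half or all of that change is reached by week 4 and by the trigger.
- Correlation with baseline 0.5; among week 4, trigger and week 24, r = 0.5 or 0.7.
- Regression imputation within arm, one million draws per arm, no rescue effect.

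If everyone above 8 leaves (HA 11-17%, PRP 4-11%), the week-24 differences are:

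| r | Change reached | True | Imputed from baseline | Imputed from baseline + week 4 | Trigger VAS included |
|---|---|---|---|---|---|
| 0.5 | half | -0.987 | -0.941 | -0.954 | -0.988 |
| 0.5 | all | -0.990 | -0.927 | -0.946 | -0.992 |
| 0.7 | half | -0.993 | -0.907 | -0.952 | -0.995 |
| 0.7 | all | -0.991 | -0.876 | -0.939 | -0.992 |

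The largest shift is 0.991 - 0.876 = 0.115, about 0.12 point or 12%. With baseline only, the shrinkage is 5-6% at r = 0.5 and 9-12% at r = 0.7. With week 4 added it is 3-4% and 4-5%. With the trigger VAS in the model it is about 0%. The same holds when the trigger is the scheduled week-4 score and that score is used (for example, true -0.988, imputed -0.988).

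The mechanism shows in the withdrawn HA patients at r = 0.5. Their true week-24 VAS is 7.0-7.2. It is imputed as 6.0-6.2 from baseline, or 6.3-6.5 with week 4.

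**Step 4: milder cases.** If the physician withdraws only half of those above 8, the shrinkage is 2-3% (r = 0.5) and 3-5% (r = 0.7) from baseline only, and 1-2% with week 4. With baseline mean 5.5 and half leaving (HA 2-4%, PRP 1-2%), it is 1-3% from baseline only and about 1% with week 4.

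**Step 5: rescue.** Suppose everyone above 8 leaves and rescue lowers their week-24 VAS by 1 or 2 points. The as-randomised difference that continued follow-up would collect is then -0.933 to -0.925 (1 point) or -0.878 to -0.851 (2 points). The extremes against imputation are:

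- -0.879 against -0.925: 0.046/0.925 = 5% too small.
- -0.946 against -0.852: 0.094/0.852 = 11% too large.

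**Step 6: scale.** Section 2.2 plans 35 per arm with 20% dropout, so 35 × 0.8 = 28 evaluable. With SD 2, SE = 2 × √(2/28) = 0.53. The largest shift is 0.12/0.53, just under a quarter of one standard error.

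**The case against.** The best case for leaving the rule alone has four parts.

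- **The rule is narrow and discretionary.** Pain must be both unrelieved by injection and above 8, and the physician then acts only if necessary. Acute knee pain and Kellgren-Lawrence grade IV are excluded. Ground (3) is close to the ordinary right to stop, in an article whose English is rough, so a deliberate merging is uncertain. This stands as a limit on frequency. It does not change what the rule permits.
- **A VAS must be taken to apply a VAS threshold.** If it is the scheduled week-4 score, imputation deals with it. This stands, and it confines the bias to triggers that are unscheduled or left out of the model. What the case report form holds is a detail that an article may leave out, so the absence of a stated record is not itself the fault.
- **Much is already planned.** There is intention-to-treat analysis, imputation, a 20% dropout allowance and recorded reasons for withdrawal. These keep patients in the analysis and explain departures, but they do not supply the later scores.
- **Leaving may protect the patient.** A reader might infer that withdrawal after week 4 stops no treatment, because injections have ended. The document does not support that: under section 2.11 quadriceps training, with squats and increasing weights, runs through the whole study. A patient in severe pain still has a study treatment to stop. Nor does the codeine advice in section 2.9 settle how pain at month 3 is managed, since it belongs to post-injection care. Neither point requires outcome collection to end.

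**Conclusion.** The point holds as a design weakness of modest severity. Section 2.6 makes a poor value of a primary outcome, and a decision to stop treatment, grounds for ending follow-up.

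Three stronger inferences are tempting, and the document supports none of them:

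- **That the comparison is seriously biased.** The largest shift, about 0.12 point against a standard error of about 0.53, needs every patient above 8 to leave, r = 0.7, a trigger that is never recorded or used, no later score to impute from and no rescue effect. If half leave, it is about 1-5%. If the trigger is a scheduled score that enters the model, it is about 0%. Dropping all scores above 8 and comparing the observed means would give larger distortions, but that is not the planned analysis.
- **That the bias has a known direction.** Without rescue the difference shrinks. With rescue it runs from 5% too small to 11% too large.
- **That everyone above 8 must leave.** The text allows or asks, at the physician's discretion.

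All sizes rest on assumed means, SDs, correlations and leaving rates, so the bias in this trial cannot be known from the article. The reason to act is that the missing visits are avoidable.

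**What to change.** Amend section 2.6 as follows:

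- Make VAS above 8 with unrelieved pain, and a patient's decision to stop treatment, reasons to stop injections, to pause or reduce quadriceps training, or to give rescue, at the physician's discretion as now.
- Unless the patient withdraws consent to follow-up, continue VAS, WOMAC and adverse events at weeks 4, 12 and 24, record rescue use, and analyse as randomised.
- Record the triggering VAS with its date, and include it in the imputation model for anyone who still leaves.

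The cost is a few sentences and one dated VAS entry on the withdrawal form. Recruitment and treatment are under way (section 2.17), so this needs a short amendment, and it helps only patients who have not yet left. The downsides are a few extra follow-up contacts at visits already scheduled, and some later scores that reflect rescue treatment.
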